## 2 Abbreviations

---

AP: Antipsychotic  
AUDIT: Alcohol Use Disorders Identification Test  
BACS: Brief Assessment of Cognition  
BAS: Barnes Akathisia Scale  
BPRS: Brief Psychiatric Rating Scale  
CDSS: Calgary Depression Scale for Schizophrenia  
CGI-S: Clinical Global Impression Severity  
CIMS: Centre for Molecular Imaging of Sherbrooke  
DSM V-TR: Diagnostic and Statistical Manual of Mental Disorders, 5th Edition, Text Revision  
DUDIT: Drug Use Disorders Identification Test  
DUP: Duration of Untreated Psychosis  
PEP Team: First Episode of Psychosis Team  
ESS: Epworth Sleepiness Scale  
FCQ: Food Craving Questionnaire  
FTND: Fagerström Test for Nicotine Dependence  
GAF: Global Assessment of Functioning  
MARS: Medication Adherence Rating Scale  
ATP Project: Pilot Research Project Antipsychotic-PET-Psychosis  
SIMPAQ: Simple Physical Activity Questionnaire  
UKU: Side Effect Rating Scale

### 3 Project Rationale and Literature Review

---

#### The ATP Research Project (Antipsychotic-PET-Psychosis)

---

We propose to evaluate the early impacts of psychosis and antipsychotic medications (APs) on brain metabolism (glucose and ketones) in young adults recently diagnosed with a first episode of psychosis.

To do this, we will measure brain and systemic glucose and ketone metabolism before and 4 to 6 weeks after the prescription of APs.

#### Psychosis

---

Psychosis, particularly schizophrenia, is one of the most severe and difficult-to-treat mental disorders. It constitutes a global public health issue, as just under 1% of people suffer from psychosis, yet they experience severe consequences that result in a significant economic burden on society.

The diagnosis of psychosis is based on a combination of clinical arguments without relying on biomarkers, especially without signatures in brain imaging. To maintain a certain sensitivity and specificity in diagnosis, Canadian clinicians use a criterion-based manual, DSM-5-TR (American Psychiatric Association 2022). Symptoms are divided into three subcategories: positive symptoms (hallucinations, delusions, disorganization of thought and behavior), negative symptoms (alogia, affective blunting, avolition, anhedonia, asociality), and cognitive symptoms (alterations in concentration, attention, executive functions, working memory, and learning). According to expert consensus and the biopsychosocial reference model, psychosis results from a combination of biological, environmental, and psychological vulnerability factors.

The reference treatment for psychosis also follows the biopsychosocial model, with the success criterion being the improvement of symptomatology and functionality. In the biological aspect of this model, pharmacotherapy, mainly second- and third-generation APs, is the reference treatment. Alongside the biological aspect, psychosocial interventions, notably supporting the person in functional rehabilitation, are added.

Concerning the early stage of psychosis, patients experiencing a first episode of psychosis face a poor prognosis if not quickly and effectively managed, and if relapses are not prevented: learning to live with chronic psychotic symptoms, reduced treatment response, brain function decline, and ultimately, a decrease in quality of life and a loss of more than 10 to 20 years of life expectancy.

#### Psychotic Disorders and Metabolic Impacts

---

People with psychotic disorders are twice as likely to die from cardiovascular accidents and have a fourfold higher risk of obesity. APs have significant metabolic side effects, such as weight gain and altered glucose and lipid homeostasis. This increases the risk of developing obesity, type 2 diabetes, and cardiovascular diseases. Moreover, some researchers have shown a positive association between symptom improvement after taking APs and metabolic disturbances, although this link remains controversial. Nonetheless, this suggests common mechanisms between the action of APs and their side effects.

It is generally accepted that interventions aimed at combating these metabolic side effects (notably by prescribing oral antidiabetics to improve insulin sensitivity) do not worsen psychiatric symptoms.

Regarding nutritional interventions, although this is a promising field, few interventions focus on the evaluation and management of the nutritional and metabolic aspects of these patients. Furthermore, weight gain induced by APs is one of the most burdensome side effects and often leads to discontinuation of treatment.

It is important to note that patients experiencing a first episode of psychosis already exhibit certain glucose homeostasis disturbances, such as insulin resistance or prediabetes, even before starting APs. This metabolic disruption could, therefore, be intrinsic to psychotic disorders, independent of the metabolic effect of APs. A meta-analysis comparing AP-naïve patients with glucose dysregulation without psychiatric illness concluded that both groups exhibit a similar gene expression signature. A second meta-analysis focusing on obesity markers also demonstrated a difference between healthy controls and AP-naïve psychotic patients experiencing a first episode of psychosis. Several aspects of brain energy metabolism may be disrupted in psychotic disorders, such as insulin and glucose signaling, glycolysis, astrocyte-neuron coupling, and ATP production by brain cells.

Studies have also linked negative and cognitive symptoms to glucose metabolism dysfunction in the prefrontal cortex, particularly in patients with schizophrenia and who are AP-naïve.

However, according to our review of the literature, there is no data regarding ketone metabolism, the brain's main alternative fuel to glucose, in patients with psychosis.

Some authors have thus proposed that psychotic disorders could be seen as a disruption of systemic and brain energy metabolism. Moreover, these metabolic disruptions could be intrinsic to psychotic disorders, just like the psychiatric symptoms that define these diseases. Thus, the pathophysiology of psychotic disorders could contribute to glucose dysregulation in addition to the deleterious effect of APs. Hence the importance of studies measuring brain metabolism (glucose and ketones) before and after the prescription of APs. However, more data is needed to fully understand the mechanisms related to these disruptions, particularly at the onset of the disease and especially in the brain itself.

It is also important to note that both psychosis and metabolic disorders, such as obesity, dyslipidemia, and type 2 diabetes, are associated with cognitive disorders. Their exacerbation during aging has been little studied and remains to be clarified.

### The Program for First Episodes of Psychosis

---

The CIUSSS de l'Estrie-CHUS and its psychiatry department have their own PEP (First Episode Psychosis) program, known as the PEP Team of Estrie. One of the unique features of accessing this team is that it does not require a medical consultation request. This allows for accelerated follow-ups, with a team leader who analyzes all requests within 24 to 72 hours, performs an initial screening of the requests, and then refers them to a psychiatrist. The timeframe for conducting a psychiatric evaluation is approximately 7 to 10 days. If the person meets the program's eligibility criteria, a joint follow-up between the psychiatrist and a psychosocial worker will begin.

PEP programs offer flexible multidisciplinary follow-up for up to 3 years. To benefit from a PEP team, participants must have never been treated for psychosis for more than 12 months. This specialized program aims to reduce the duration of untreated psychosis and minimize its effects, enabling a return to normal functional development and optimal, sustained recovery over time.

## Medical Imaging for the Study of Metabolism

---

Magnetic resonance imaging (MRI) is the gold standard for imaging psychiatric disorders, but it is mainly used to exclude neurological disorders. In clinical practice, brain imaging is not routinely recommended for people with psychosis that appears before the age of 45, unless there are clinical signs suggesting a neurological problem. As explained earlier, there is no imaging signature or biomarker for psychosis.

To study brain energy metabolism, the addition of quantitative positron emission tomography (PET) with metabolic radiotracers for glucose and ketones (FDG-glucose, 11C-Acetoacetate, 11C-Acetate, etc.) allows for much greater insights. Our team in Sherbrooke was the first to develop the 11C-Acetoacetate tracer to visualize brain ketone uptake, and has thus developed expertise in multi-imaging approaches, combining multi-tracer PET with various MRI modalities (volumetric, functional, diffusion, etc.). Our 15 years of experience in metabolic medical imaging has allowed us to establish a comprehensive multimodal database, including controls of young adults in the same age group as individuals experiencing a first episode of psychosis.

These tools have enabled us to demonstrate in older individuals that, unlike the energy deficit in glucose, ketone uptake and utilization do not decrease with age or with the onset of cognitive decline. Furthermore, increasing plasma ketones through ketogenic supplementation can boost brain fuel supply and largely compensate for the energy deficit in individuals with mild cognitive impairment, the prodromal stage of Alzheimer's disease. This fuel supply could even have a functional impact by improving various cognitive functions. Other conditions with metabolic dysregulation, such as Parkinson's disease and other medical conditions (heart failure, polycystic ovary syndrome, renal failure, etc.), have been or are being studied by our team to better understand the energy deficit in different organs in various diseases, inspiring the development of innovative therapeutic approaches.

To our knowledge, no PET study of brain energy metabolism (glucose and ketones) has been conducted in patients experiencing a first episode of psychosis.

## Conclusion

---

Our expertise in medical imaging will allow us to evaluate and quantify changes in brain energy metabolism at the onset of psychotic illness, before and after the introduction of APs, thereby better understanding the differentiated impacts of the disease and medication on metabolic disturbances. This improved understanding may eventually lead to the development of better treatments for these patients, encompassing the metabolic aspects of the disease.

## 4 Research questions and objectives

---

### Research Question and Hypothesis

---

To evaluate the effect of psychosis and the initiation of antipsychotic medication during a first episode of psychosis on brain energy metabolism. The hypothesis is that patients with a first episode of psychosis (PEP) will exhibit frontal glucose hypometabolism, and we expect this to worsen with antipsychotic medication. We expect no changes in ketone metabolism.

### Primary Objective

---

In patients with a first episode of psychosis, evaluate the effect of 4 to 6 weeks of antipsychotic medication on brain metabolism measured by PET scan (cerebral uptake of 11C-Acetoacetate + 18 Fluorodeoxyglucose).

### Secondary Objectives

---

- 1) In patients with a first episode of psychosis, compare the effect of 4 to 6 weeks of antipsychotic medication on brain metabolism measured by PET scan (cerebral uptake of 11C-Acetoacetate + 18 Fluorodeoxyglucose) to clinical improvement (measured by the percentage change in the Brief Psychiatric Rating Scale) and systemic metabolism (measured by continuous glucose monitoring).
- 2) Compare brain fuel utilization measured by PET scan (cerebral uptake of 11C-Acetoacetate + 18 Fluorodeoxyglucose) between AP-naïve patients with a first episode of psychosis and an existing dataset of healthy controls (matched for age and sex).

### Exploratory Objectives

---

Examine associations before and during AP treatment with other measures of psychopathology (e.g., cognition, depressive symptoms, etc.) and metabolism (weight, lipids, inflammation markers, etc.), general systemic impact (renal, hepatic function, inflammation, etc.), and brain structure (MRI).

Compare continuous glucose monitoring data to plasma glucose metabolism measures, as well as the acceptability and feasibility of this monitoring.

## 5 Study Population

---

### Target Population:

Individuals aged 18 to 35 from the Estrie region who have been evaluated by the PEP team and wish to start an antipsychotic (AP) for the treatment of a first episode of psychosis.

### 5.1 Sample Size

---

This is a pilot observational study. Currently, there are no studies that have measured cerebral use of 11C-Acetoacetate before and after AP administration. We must rely on our previous studies on energy metabolism, which showed differences in the same variables with groups of 7 to 15 participants.

Number of participants: 18 participants to reach 10 who complete the study. This pilot study will allow us to obtain preliminary data to secure funding for future studies.

### 5.2 Inclusion Criteria

---

- Individuals aged 18 to 35.
- Admission to the PEP clinic in Estrie, either outpatient or inpatient, according to the transdiagnostic PEP model.
- Willingness to begin taking an AP (regardless of type and dose, or change in type and dose during the study).
- Ability to read and express themselves in French or English.
- Capable of understanding and signing consent.

### 5.3 Exclusion Criteria

---

- Pregnancy, childbirth in the last 6 months, or breastfeeding.
- Presence of a metallic object in the body that is incompatible with MRI.
- Any use of APs for more than 2 continuous weeks in the past year and/or 6 weeks in a lifetime (except for aripiprazole if taken at less than 2.5 mg/day or quetiapine at less than 50 mg/day, regardless of duration or timing of the prescription).
- The following comorbidities: psychosis + borderline or intellectual disability, autism spectrum disorder, substance use disorder with decompensation, psychosis induced by a medical condition, or psychosis induced by drug use or withdrawal.
- Type 1 diabetes.
- Uncontrolled acute suicidal ideation.
- Other conditions that could interfere with participation according to the judgment of the qualified physician.

### 5.4 Withdrawal Criteria During the Study

---

The participant's participation in the research may be terminated by the responsible researchers or the participant themselves. This will occur if new discoveries or information indicate that participation in the study is no longer in the participant's best interest, if it becomes apparent that the participant is not following the study's guidelines, or if there are administrative reasons to abandon the study.

Definitive withdrawal from the study will occur in the following cases:

- Voluntary withdrawal. A participant may withdraw their consent to participate in the research at any time without affecting the services and treatments offered.
- Inability to complete initial visits within the 10-day timeframe.
- Initiation of AP medication (other than what is permitted under concomitant medication below) before completing the 2 "BEFORE" visits (depending on the participant's desire or clinical changes).
- Any changes deemed by the responsible physician to be contraindications to continuing in the study (significant renal or hepatic insufficiency, etc.).

### 5.5 Concomitant Medication

---

#### **Period before the "V2- Imaging BEFORE" visit**

Typically, during the evaluation period at the PEP clinic before the introduction of an antipsychotic at antipsychotic doses, a "non-AP dose" medication may be prescribed to treat certain symptoms (distress, sleep) and will be accepted as part of the study. This includes:

- Quetiapine 12.5 mg to 50 mg PO HS PRN.

An anxiolytic may also be prescribed for imaging:

- Alprazolam 0.25 to 0.5 mg PO BID PRN.

#### **Period between the "V2- Imaging BEFORE" visit and the 2 final visits**

Any medication prescribed by the treating team (e.g., to treat side effects, etc.) or taken over the counter by the participant will not result in exclusion but will be documented.

## 6 Research Methodology

### 6.1 Study Duration

Total projected duration of the project: 18 months

Recruitment period duration: 16 months

Projected participation duration for participants: Between 5 and 7 weeks

### 6.2 Recruitment

Participants will be among the newly admitted patients to the PEP program of the Psychiatry Department of CIUSSS de l'Estrie-CHUS. Only patients for whom a psychiatrist deems it appropriate and safe to undergo tests before starting an AP will be invited to participate. After identifying a potentially eligible patient by a psychiatrist, a member of the PEP team or the doctor will ask for permission to be contacted for research participation. Then, a member of the research team (researcher or research professional) will contact the person to present the project and obtain their consent.

### 6.3 Summary of the study

| Table 1. Summary of study procedure                      | min | Eligibility | PRE        | TEP pre    | POST        | TEP post    |
|----------------------------------------------------------|-----|-------------|------------|------------|-------------|-------------|
| Weeks since admission to clinique PEP             |     | 0-1  | 0-1 | 0-1 | 6-10 | 6-10 |
| Consent                                                  | 15  | X           |            |            |             |             |
| Blood test                                               | 5   |             | x          |            | x           |             |
| Physical measure                                         | 10  |             | X          |            | X           |             |
| MRI eligibility questionnaire                            | 2   | X           |            | X          |             | X           |
| Prenancy test                                            | 2   | x           |            | X          |             | X           |
| DUP                                                      | 2   | X           | X          |            |             |             |
| Brief Psychiatric Rating Scale (BPRS)             | 15  |             | X          |            | X           |             |
| Clinical Global Impression, Severity (CGI-S)      | 5   |             | X          |            | X           |             |
| Calgary Depression Scale for Schizophrenia (CDSS) | 10  |             | X          |            | X           |             |
| Global Assessment of Functioning (GAF)            | 2   |             | X          |            | X           |             |
| Brief Assessment of Cognition (BACS)              | 30  |             | X          |            | X           |             |
| Side Effect Rating Scale (UKU)                    | 20  |             | X          |            | X           |             |
| Alcohol Use Disorders Identification Test (AUDIT) | 2   |             | X          |            | X           |             |
| Drug Disorders Identification Test (DUDIT Drug)   | 2   |             | X          |            | X           |             |
| Fagerström Test for Nicotine Dependence (FTND)    | 2   |             | X          |            | X           |             |
| Sleepiness Scale (ESS)                            | 1   |             | X          |            | X           |             |
| Simple Physical Activity-questionnaire (SIMPAQ)   | 5   |             | X          |            | X           |             |
| Barnes akathisia scale (BAS)                      | 2   |             |            | X          |             | X           |
| Food Craving questionnaire (FCQ)                  | 5   |             |            | X          |             | X           |
| Medication list (type + dose)                     | 2   | X           |            |            | X           |             |

|                                       |     |  |  |   |   |   |
|---------------------------------------|-----|--|--|---|---|---|
| Adherence questionnaire (MARS) | 2   |  |  |   | X |   |
| PET scan                              | 120 |  |  | X |   | X |
| MRI                                   | 30  |  |  | X |   |   |
| Continuous glucose monitoring         | 15  |  |  | X |   | X |

## 6.4 Study Procedures

---

After the eligibility visit (V0-eligibility), the participant will be invited to complete the V1-clinical and V2-PET visits before starting the medication (“BEFORE”), but no later than 10 days after the first visit with the psychiatrist.

The two other visits, V3-clinical and V4-PET, will occur 4 to 6 weeks “AFTER” the start of antipsychotic medication.

### V0-Eligibility Visit

---

Location: Hôtel-Dieu

Duration: 1 hour

#### Procedure:

The participant is invited to a brief meeting with a research team member after one of their weekly hospital visits or at their convenience. After presenting the information and consent form and obtaining the signature, various questionnaires will be completed. A snack will be provided.

- Verification of eligibility criteria.
- Sociodemographic data questionnaire.
- Medication list.
- MRI contraindication questionnaire.
- Planning of subsequent visits.

### V1 and V3 Clinical Visits (BEFORE and AFTER)

---

Location: Hôtel-Dieu

Duration: 2 hours

#### Procedure:

- Fasting Blood Draw: 12 hours fasting required.
- Meal/snack provided after blood draw.
- Measurements: Weight, height, waist circumference.
- Blood pressure and pulse.
- Questionnaires will be done as listed in Table 1.
- Breaks will be offered to the participant (snack, coffee).

### V2 and V4 Imaging Visits (BEFORE and AFTER)

---

Location: Centre for Molecular Imaging of Sherbrooke (CHUS Fleurimont)

Duration: 3 hours (fasting for 4 hours before)

#### Procedure:

- Reconfirm consent.
- Verification of MRI contraindication questionnaire.
- Pregnancy Test
- 15 minutes MRI Scan (volumetric and vascular system imaging).
- Two intravenous catheters will be installed in the forearms, and blood glucose will be measured.
- 20 minutes PET Scan with 11C-Acetoacetate with blood sampling.
- Break: 40 minutes break.
- 30 minutes PET Scan with 18F-FDG with blood sampling.
- Snack provided after the imaging session.

#### Continuous Glucose Monitoring (Optional)

---

At the end of the imaging visit, the continuous glucose monitor (Dexcom G7) will be applied, and instructions will be provided (synchronization period, precautions for bathing, etc.). The device will be removed between 8 and 10 days later, according to what suits the participant best.

The compatibility of the device with the participant's mobile phone will be verified, and their agreement will be obtained to install the application.

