##### **Blood test - metabolism**

- General panel\*: Complete blood count, renal function (creatinine), liver function (AST, albumin), thyroid function (TSH), inflammation marker (C-reactive protein).
- Metabolic profile (glucose, insulin, hemoglobin A1c, triglycerides, cholesterol, lactate, insulin, ketones\*\*).
- Metabolomics.
- Cytokines.
- Inflammatory profiles.

\*Upon admission to the PEP clinic, a general panel is performed (CBC, TSH, basic liver panel, basic renal panel, sodium, potassium, lipid profile, HbA1c). If the results are already available in the medical record, the panel will not be repeated during the "BEFORE" visit.

\*\*Certain analyses will be conducted in [name] laboratory. Plasma will be frozen for some analyses to be performed at a later time.

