### Continuous Glucose Monitoring

---

Glucose levels will be monitored using a continuous glucose monitor (Dexcom G7). This portable device features a small disposable sensor that tests glucose levels every five minutes and sends this information

to a transmitter throughout the day and night. The readings are relayed in real-time to a device that can be read by the patient, caregiver, or healthcare provider, even remotely.

The sensor is worn under the skin (often on the abdomen or arm). The sensor will be placed by the nurse during the metabolic visit, and glucose values will be recorded for about 10 days (8 to 12). The participant will wear a sensor at two points during the project: at the beginning and the end of the study.

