**Secondary variables related to systemic metabolism:**

- Plasma glucose concentrations (mM);
- Plasma insulin concentrations (pM);
- Plasma HbA1c concentration (%);
- HOMA-IR score.

**Secondary variables related to changes in cerebral energy metabolism in a healthy control group matched by age and sex ([name] database):**

- Cerebral metabolic rate of glucose ( $\mu\text{mol}/100 \text{ g/min}$ ) quantified with 18F-FDG;
- Net glucose influx with 18F-FDG (Kglu; min);
- Cerebral metabolic rate of acetoacetate with 11C-AcAc ( $\mu\text{mol}/100 \text{ g/min}$ );
- Net acetoacetate influx with 18F-FDG (Kglu; min).

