**Exploratory variables related to continuous glucose monitoring:**

- Average glucose concentration;
- Standard deviation and coefficient of variation;
- Time in range.

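### The protocol does not ensure that the BEFORE continuous glucose record is pre-treatment, and secondary objective 1 and the variable list disagree on whether that record is the secondary systemic measure

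*Protocol*

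**What the plan says.** **Placement and wear.** Section 6.4 (Continuous Glucose Monitoring, optional) states: "At the end of the imaging visit, the continuous glucose monitor (Dexcom G7) will be applied". It adds: "The device will be removed between 8 and 10 days later, according to what suits the participant best". Table 1 in section 6.3 agrees, marking the sensor in the two PET columns. Section 6.6 differs: "The sensor will be placed by the nurse during the metabolic visit". No visit of that name is defined elsewhere, and section 6.6 gives a wear time of about 10 days, range 8 to 12.

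**Order of visits and treatment.** Under section 6.4 the participant "will be invited to complete the V1-clinical and V2-PET visits before starting the medication", within 10 days of the first psychiatric consultation. Section 5.4 withdraws anyone who starts an antipsychotic, beyond the permitted concomitant use, before those two visits are done. Neither section mentions sensor wear. Section 7.1 describes about 7 days to treatment in usual practice, a possible further 2 to 3 days for the BEFORE imaging, and clinical experience that most patients ask to begin at an appointment two weeks later.

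**Role of the sensor.** Secondary objective 1 (section 4) relates the PET change to clinical improvement and to "systemic metabolism (measured by continuous glucose monitoring". In section 8.2, the list titled "Secondary variables related to systemic metabolism" holds plasma glucose, insulin, HbA1c and HOMA-IR, with no sensor variable. The sensor summaries appear under "Exploratory variables related to continuous glucose monitoring". Sections 6.4 and 7.11 make the sensor optional.

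**The concern.** V2 is the last visit that must come before treatment, and the sensor goes on only when V2 ends. Every day of the BEFORE record therefore lies in the period when treatment may begin. Section 8.1 plans paired BEFORE-AFTER tests and correlations of metabolic with clinical and brain measures. If some BEFORE days are on treatment, the sensor contrast is partly treated against treated rather than untreated against treated, and the mixture differs by participant. With 10 completers intended (section 5.1) and an optional device, there is little room to absorb that.

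The second problem is independent of timing. The objective and the variable list assign the secondary role to different measurements, so the protocol does not settle which result answers objective 1.

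**Working it through.** The protocol gives no figure to reproduce here, so the check is timeline arithmetic.

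**Inputs.** Day 0 is the first psychiatric consultation. V2 falls on day v, from 1 to 10 (section 6.4). Treatment starts on day s, at or after V2. I take s = 7 and s = 10 (7 days, plus up to 3 more) and s = 14 (the two-week case), all from section 7.1. Wear time w is 8, 10 or 12 days (sections 6.4 and 6.6).

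**Formula.** Untreated share of the BEFORE record = min(w, s − v) / w.

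| Start day s | V2 day v | Days from V2 to start | w = 8 | w = 10 | w = 12 |
|---|---|---|---|---|---|
| 7 | 1 | 6 | 75% | 60% | 50% |
| 7 | 3 | 4 | 50% | 40% | 33% |
| 7 | 7 | 0 | 0% | 0% | 0% |
| 10 | 1 | 9 | 100% | 90% | 75% |
| 10 | 2 | 8 | 100% | 80% | 67% |
| 10 | 7 | 3 | 38% | 30% | 25% |
| 10 | 10 | 0 | 0% | 0% | 0% |
| 14 | 2 | 12 | 100% | 100% | 100% |
| 14 | 4 | 10 | 100% | 100% | 83% |
| 14 | 6 | 8 | 100% | 80% | 67% |
| 14 | 10 | 4 | 50% | 40% | 33% |

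**Reading the table.**
- Start on day 7: no V2 day gives a wholly untreated record at any wear time.
- Start on day 10: an 8-day record is wholly untreated only with V2 on day 1 or 2; a 10- or 12-day record never is.
- Start on day 14: the record is wholly untreated if V2 is by day 6 (8-day wear), day 4 (10-day wear) or day 2 (12-day wear).

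**Which start day does the protocol imply?** It points both ways. Section 6.1 gives 5 to 7 weeks of participation, and section 6.4 puts the AFTER visits 4 to 6 weeks after treatment start. Matching the ends, 5 − 4 = 1 and 7 − 6 = 1, so about one week from entry to start, which is shorter than the 8-day minimum wear. Table 1 puts the AFTER visits at weeks 6 to 10 since clinic admission: 6 − 4 = 2 and 10 − 6 = 4, so a start two to four weeks after admission. No section fixes the interval from V2 to first dose.

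**Effect on the contrast.** Let f be the untreated share and D the true effect on mean glucose. Assume, for illustration, that the effect is immediate and constant and that the AFTER record is wholly on treatment. The BEFORE mean is then baseline + (1 − f)D and the AFTER mean is baseline + D, so the observed change is fD. At f = 0.6, 60% of the effect is seen; at f = 0.3, 30%. Two participants with the same D but f = 0.6 and f = 0.1 would show changes of 0.6D and 0.1D, a difference produced by scheduling alone. A slower onset loses less. The formula does not carry over to the standard deviation or coefficient of variation, which do not average linearly over mixed days.

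**Role of the sensor.** Set side by side, the section 4 objective makes the sensor the measure of systemic metabolism, while section 8.2 places it in the exploratory tier and four plasma measures in the secondary tier. Both cannot stand.

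**The case against.** The strongest reply has four parts.

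- **A baseline exists.** A reader might infer that secondary objective 1 lacks any pre-treatment systemic baseline. It does not. V1 includes a 12-hour fasting draw before treatment, and it supplies the plasma variables that section 8.2 calls secondary. What is missing is an assured pre-treatment baseline for the measure that the objective itself names.
- **Overlap is not certain.** A reader might also infer that at least 30% of BEFORE readings must be on treatment. That follows only if the two-week case is worked with V2 on day 7 (7 of 10 days untreated). With V2 by day 4 the on-treatment share of a 10-day record is zero. This part stands: the range is 0 to 100%.
- **It can be handled in analysis.** The sensor reads every five minutes, and the start date must be known because V3 and V4 are timed from it. An analysis plan not shown here could restrict BEFORE data to pre-dose readings. That is fair, and it shows that the remedy is easy. But the protocol itself sets a placement that allows the overlap, and the conflict between sections 4 and 8.2 is not analysis detail.
- **It is a pilot.** The sensor is optional and partly there to test acceptability and feasibility. The primary PET variables are unaffected.

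A further tempting reading is that the laboratory baseline has the same defect, because of the admission panel section 6.6 says: "If the results are already available in the medical record, the panel will not be repeated during the" BEFORE visit. The documents do not support that. Admission results are also pre-treatment, HbA1c does not depend on fasting, and C-reactive protein is not on the admission list, so that list does not waive it. Only the lipids, which are exploratory, could be taken at baseline without a stated fast.

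**Conclusion.** The point holds in two parts. First, the protocol does not ensure that the BEFORE sensor record is pre-treatment. On a 7- to 10-day schedule the record would usually mix untreated and treated days; with an early V2 and a start at about two weeks it can be clean. The attenuation depends on how quickly treatment affects glucose, which the documents do not give; the proportional loss above is an illustration under an immediate, constant effect. Second, secondary objective 1 contradicts section 8.2 on which measure is secondary. Sections 7.11 and 8.2 agree with each other, so the objective is the outlier.

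The difference between sections 6.4 and 6.6 is smaller: an undefined visit label and a different wear range. It does not establish that a different visit was meant.

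This should be corrected, preferably before enrolment. It concerns an optional measure in a pilot, leaves the primary comparison intact, and is not grounds to hold up the study.

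**What to change.** 1. **Define the BEFORE record.** Record the date and time of the first antipsychotic dose, using the same start from which V3 and V4 are timed. Define BEFORE sensor data as readings before that dose, state a minimum number of valid days, and label later days early treatment. Clinical timing is unchanged. Cost: one data field and a sentence or two. Downside: fewer usable BEFORE days, and none for some participants.
2. **Align section 4 with section 8.2.** Name in secondary objective 1 a plasma measure planned for all participants, such as HOMA-IR, and keep the sensor exploratory. Cost: wording only.
3. **Reconcile sections 6.4 and 6.6** on the placement visit and the wear time. Cost: wording only.
4. **Optional:** measure the exploratory lipids on the V1 fasting draw in everyone. Cost: a few assays on blood already being drawn.

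Applying the sensor at V0 or V1 would lengthen the untreated record, but the protocol says nothing about wearing it through MRI or PET, so I do not recommend it on this evidence.
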